### Safety concern

Subjects will be provided with sufficient information regarding the potential adverse events of benzodiazepine withdrawal. Benzodiazepine withdrawal symptoms, and electroacupuncture-related adverse events will be assessed at each study visit. Benzodiazepine withdrawal symptoms will be assessed by the BWSQ. A standardized electroacupuncture-related adverse event form [42, 43], consisting of eight items on adverse events around the needle sites, 13 items on systemic adverse events, and three items on serious adverse events, will be used. Severity of each adverse event will be rated as “absent”, “mild”, “moderate” or “severe” and the causality of adverse event will be reported using a 5-point Likert scale, ranging from “unrelated” to “certain”. In addition, worsening of pre-existing medical and psychiatric conditions is counted as adverse events. Subjects with heart rate over 100 beats per minute, systolic blood pressure higher than 140 mmHg, diastolic blood pressure higher than 90 mmHg, and any suicidal risk based on the HDRS suicidality item will be evaluated by the Principal Investigator before continuing in the study. Those with moderate suicidal risk will be excluded from the study and referred to their case doctors as early as possible.

### Blinding assessment

As all outcome measures are self-reported, assessments are deemed to be blinded. Success of participant blinding will be measured at the last electroacupuncture session. Subjects will be asked a standard question: “When you volunteered for the trial, you were informed that you would receive traditional acupuncture, or acupuncture-like placebo treatment. Which acupuncture do you think you received?” The standard question is adapted from the paper by Park et al. [44].

### Sample size calculation

Sample size calculation is based on benzodiazepine cessation rate, the primary outcome. No previous studies have been conducted on the efficacy of electroacupuncture and placebo electroacupuncture for tapering benzodiazepines; hence the effect size for sample size calculation is estimated according to previous randomized controlled trials using psychological intervention. A median cessation rate of 74% (range = 13–85%) was reported in a previous systematic review on benzodiazepine tapering using psychological intervention [11]. We estimate that electroacupuncture will produce a cessation rate similar to that of psychological intervention (75%) and the cessation rate in placebo control group is about 50%; hence. a 25% difference in cessation rate between groups is assumed [27]. A power of 80% has been regarded as a reasonable protection against Type II error [45]. Based on a 25% between-group difference and a power of 80%, the minimal number of subjects that are required to avoid a Type I error of 0.05 is 108 (54 per group). The final sample size is 144 (72 per group) after allowing a 25% attrition rate at 12-week posttreatment.

### Statistical analysis

Data will be double-entered and checked for consistency. Data analysis will be performed with an identification code of group A and group B according to a pre-specified statistical analysis plan. The coding of group allocation will be revealed after the completion of data analysis or in case of reports of serious adverse events associated with electroacupuncture or benzodiazepine withdrawal. Between-group difference will be assessed by two-sample t-test or chi-square test at baseline, week 4 (end of treatment), week 6 (2-week posttreatment), and week 16 (12-week posttreatment). The absolute risk reduction and number of subjects that are needed to be treated to obtain one benzodiazepine withdrawal will be estimated at week 16. Attempts will be made for minimizing missing data among subjects who do not return for assessment or have withdrawn from study by mail and phone reminders. Both per protocol and intention-to-treat analyses will be performed. Multiple imputation technique will be used to handle missing values, assuming data are missing at random (MAR). Ten sets of imputed values will be generated to adjust for variability due to imputation, and so ten completed data sets will be created. These completed data sets will be analyzed separately with standard statistical methods, and the results are combined into a single multiple-imputation result [46]. Sensitivity analysis will be conducted to examine the effect of departures from the assumption of MAR on clinical outcomes. The missing data due to dropout cases may be associated with those who rebound in insomnia or anxiety levels, or those who fail to decrease consumption of benzodiazepine. Pattern mixture models with various possible values of the informative missing parameters will be employed to conduct the sensitivity analysis [47]. For dichotomous outcomes, the informative missing parameter specifies the odds ratio between the outcome and missingness indicator. For continuous outcomes, it specifies the mean difference between the unobserved outcome and observed outcome. By varying the informative missing parameter, it is possible to examine the magnitude of departures from MAR assumption on different outcomes. Stata rctmiss will be used to do the sensitivity analysis [48].

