### Outcome measures (Table 3)

#### Primary outcome

Primary outcome is the proportion of participants who successfully discontinue benzodiazepines at 2-week posttreatment (week 6) and 12-week posttreatment (week 16). Previous randomized controlled trials of benzodiazepine tapering [10] have used cessation rate as the main outcome measure. The primary end-point is 12-week posttreatment (Fig. 2).

**Table 3 Tab3:** Summary of outcome measures and assessment schedule

Measure	Baseline	Intervention				2-week posttreatment	12-week posttreatment
		2nd	4th	6th	8th		
BZ cessation rate^a^	✓					✓	✓
BZ dose reduction, %	✓	✓	✓	✓	✓	✓	✓
BWSQ	✓	✓	✓	✓	✓	✓	✓
ISI	✓		✓			✓	✓
HADS	✓		✓			✓	✓
SDS	✓						
CTRS	✓	✓			✓		
AE monitoring		✓	✓	✓	✓	✓	✓

*BZ* Benzodiazepine, *BWSQ* Benzodiazepine Withdrawal Symptom Questionnaire, *ISI* Insomnia Severity Index, *HADS* Hospital Anxiety and Depression Scale, *SDS* Substance Dependence Scale, *CTRS* Credibility of Treatment Rating Scale, *AE* adverse events

^a^Primary outcome

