#### Secondary outcomes

Secondary measures include percentage benzodiazepine dose reduction, Benzodiazepine Withdrawal Symptom Questionnaire (BWSD), Insomnia Severity Index (ISI), and HADS. A daily dose of benzodiazepine in diazepam equivalent and percentage reduction as compared to baseline will be derived from a 14-day record form. Previous studies have suggested that prospective usage diary is more accurate than retrospective recall of consumption [34, 35]. The subject will be asked to bring back their un-used medications at each visit for cross-checking with the usage record.

Benzodiazepine withdrawal symptoms will be assessed by the 20-item self-administrated BWSQ [32]. The items include main symptoms experienced during withdrawal from benzodiazepine dependent patients including dizziness, pains in muscle, muscle twitching, and so on [32]. Withdrawal symptoms are rated as “absent”, “moderate” or “severe” (0, 1, or 2), yielding a total score ranging between 0 and 40. The original English version has been translated into Chinese for use in this study. The back-translated version has been compared with the original version to ensure it appropriately reflects the original version. Insomnia, one of the most common benzodiazepine withdrawal symptoms, will be further evaluated by the ISI [36]. The ISI is a 7-item 5-point self-rating Likert scale to indicate subjects’ perceived severity of insomnia symptoms. The total score ranges from 0 to 28. The Chinese version of ISI has been demonstrated to have adequate validity and reliability [37]. The HADS [25], a validated and widely-used self-reported questionnaire, will be adopted to measure the severity of depressive and anxiety symptoms. It consists of 14 items; seven of them are on depression and seven on anxiety, which generates the anxiety and depression subscales. Somatic symptoms are not included in the HADS. The validated Chinese version of HADS will be used in the present study [38].

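### The symptom scales (BWSQ, ISI, HADS) are to be compared by unadjusted t-tests although their baseline scores are collected: valid, but precision is given away that ANCOVA would recover at no cost

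*Protocol article*

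**What the plan says.** The Statistical analysis section of the protocol article fixes the method of comparison in one sentence: "Between-group difference will be assessed by two-sample t-test or chi-square test at baseline", then at week 4, week 6 and week 16. No model and no covariate is named.

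Table 3 (Outcome measures) schedules the BWSQ, ISI, HADS, SDS and benzodiazepine dose at baseline. The BWSQ is repeated at the second, fourth, sixth and eighth sessions, ISI and HADS at the fourth session, and all three at weeks 6 and 16. Dose change is analysed as a "percentage reduction as compared to baseline".

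The primary outcome is binary cessation, with week 16 as the primary end-point. For it the section also plans an effect estimate: "The absolute risk reduction and number of subjects that are needed to be treated to obtain one benzodiazepine withdrawal will be estimated at week 16". Missing values are multiply imputed ten times, and of the imputed sets it says: "These completed data sets will be analyzed separately with standard statistical methods, and the results are combined into a single multiple-imputation result".

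**The concern.** For a scale measured before randomization and again at follow-up, part of the follow-up variance is explained by where each participant started. A two-sample t-test on follow-up scores leaves that part in the error term. Conditioning on the baseline score removes it, and no extra data are needed because Table 3 already collects the score.

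What is at stake is the width of the confidence intervals, and hence the power, for the three symptom scales. The trial was sized on cessation alone, so nothing in the design protects power on these secondary outcomes.

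Two smaller matters sit in the same sentence. Baseline is listed among the tested time points. After random allocation the null hypothesis there is true by design, so such a test tells the reader nothing about the comparison. And the primary test named, chi-square, stands apart from the risk difference that the same section plans to report. The test, the interval and the number needed to treat would fit together better if all came from one pooled estimate.

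**Working it through.** **Inputs from the article.** 72 per group, 25% attrition at week 16, cessation 75% v 50%, power 80%, type I error 0.05 (sidedness not stated; two-sided taken here). **Assumed, not in the article.** The baseline-to-follow-up correlation r (0.3, 0.5, 0.7) and a standardized difference d for a symptom scale.

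**The plan's own figure.** Unadjusted two-proportion formula, unpooled variance:
(0.75×0.25 + 0.50×0.50) × (1.960 + 0.842)² / 0.25² = 0.4375 × 7.849 / 0.0625 = 54.94 per group, against 54 stated. Then 108 / 0.75 = 144, and 72 × 0.75 = 54 evaluable per group. The sizing is reproduced to within one participant per group and was done for an unadjusted comparison of the primary outcome.

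**Gain on the symptom scales.** Adjusting for baseline multiplies the error variance by 1 − r². The equivalent gain in sample size is 1/(1 − r²) − 1. Power by normal approximation with n = 54 per group is Φ( d·√(n/2) / √(1 − r²) − 1.96 ). For d = 0.4, d·√27 = 2.078.

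| r | 1 − r² | variance saved | worth in participants | 54 unadjusted equals, adjusted | power, d = 0.4 |
|---|---|---|---|---|---|
| 0 (t-test) | 1 | – | – | 54 | Φ(2.078 − 1.96) = 0.547 |
| 0.3 | 0.91 | 9% | +10% | 49.1 | Φ(2.179 − 1.96) = 0.587 |
| 0.5 | 0.75 | 25% | +33% | 40.5 | Φ(2.400 − 1.96) = 0.670 |
| 0.7 | 0.51 | 51% | +96% | 27.5 | Φ(2.911 − 1.96) = 0.829 |

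The choice of d does not drive the conclusion. Take instead the effect that has exactly 80% power unadjusted: d = 2.802 × √(2/54) = 0.539. ANCOVA then gives Φ(2.802/√(1 − r²) − 1.96), which is about 84%, 90% and 98% for r = 0.3, 0.5 and 0.7.

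**Which r is plausible for which scale.** The Exclusion criteria remove anyone scoring 8 or more on either HADS subscale. That truncates the baseline range and tends to lower its correlation with follow-up, so HADS may sit near the first adjusted row. No such cap applies to the BWSQ or ISI.

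**Cessation.** Everyone is a user at entry (Trial procedure), so the outcome has no baseline value that varies. Baseline diazepam-equivalent dose and SDS can still serve as covariates. No gain is calculated, because the article gives nothing on how strongly they predict cessation.

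**Pooling the binary result.** A simulation (20,000 runs, 72 per group, 25% missing completely at random, ten imputations) gave these type I error rates at nominal 0.05, with both groups at 50% and then both at 60%:

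- risk difference pooled by Rubin's rules: 0.053 and 0.055;
- chi-square statistics pooled by the D2 rule: 0.047 and 0.049;
- simple average of the ten chi-square statistics: 0.106 and 0.104.

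At 75% v 50%, power was 0.77 for the pooled risk difference and 0.76 for D2. Sound routes therefore exist, and one of them uses the quantity that the article already plans.

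**The case against.** The strongest reply is that nothing here is wrong. In a 1:1 randomized trial, unadjusted tests are unbiased and control the type I error, and the primary test matches the way the trial was sized. The figures above concern secondary outcomes that were never powered, and they rest on correlations the article does not give. All of that stands. It limits the point to efficiency, but it does not remove it: the article states the unadjusted method outright, and the baseline scores are already scheduled.

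Stronger readings are tempting, and the document does not support them.

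- **That the chi-square result cannot be combined over the imputed sets.** The article does not name Rubin's rules and does not say that a chi-square statistic is what gets pooled. A t-test mean difference and the planned absolute risk reduction both pool directly, and chi-square statistics have their own pooling rule. Which quantity is pooled is detail that the unseen statistical analysis plan may well give.
- **That baseline dose is unused.** Percentage dose reduction is defined relative to baseline, so baseline dose does enter that outcome.
- **That daily dose should be modelled in the same way as the scales.** With 50% to 75% expected to stop, percentage reduction piles up at 100%, but daily dose would pile up at zero. Treating it as a normal outcome exchanges one awkward distribution for another.
- **That the mid-treatment BWSQ readings are wasted.** They have stated uses in guiding the taper and in safety monitoring. Not testing each one is no error.

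The baseline tests are uninformative, but no stated decision depends on them and they do not affect inference on outcomes. That part is minor.

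**Conclusion.** The point holds as a loss of precision on the BWSQ, ISI and HADS. Unadjusted t-tests forgo a variance reduction of 9%, 25% or 51% if the baseline-to-follow-up correlation is 0.3, 0.5 or 0.7, equivalent to 10%, 33% or 96% more participants. The correlations are assumptions, and HADS may be at or near the low end. The planned tests remain valid and no bias is claimed.

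For cessation, adjustment for baseline dose and SDS would bring a smaller gain, which is not quantified. The benefit there is mainly coherence: one pooled estimate supplies the test, the interval and the number needed to treat. The change is worth making because it costs nothing, not because the present plan would give a wrong answer.

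**What to change.** In the Statistical analysis section (and the statistical analysis plan, if it does not already say so):

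1. **BWSQ, ISI, HADS.** Replace the t-tests by ANCOVA at each visit where the scale is scheduled, with the baseline score as covariate, or by a mixed model for repeated measures over the scheduled visits, adjusted for the baseline score. Report the adjusted mean difference with its interval. If ANCOVA is used, pool that coefficient and its standard error over the ten imputed sets.
2. **Week-16 cessation.** Fit a logistic model with group, baseline diazepam-equivalent dose and baseline SDS, and standardize it to a risk difference with its standard error in each imputed set. Pool the ten estimates and their standard errors, base the primary test on the pooled risk difference, and derive the number needed to treat from it.
3. **Baseline.** Remove baseline from the list of tested time points and describe the groups without significance tests.

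The cost is a change of wording. No new data, visits or participants are needed. The article plans no interim analysis and keeps the groups coded as A and B until the analysis is complete, so the change can be written down and dated before any outcome is analysed by group.

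### Ten imputations against a 25% attrition allowance leave avoidable Monte Carlo noise in the week-16 result: a minor reproducibility issue, fixed by raising the number

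*Protocol article*

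**What the plan says.** In the protocol article, the Statistical analysis section plans multiple imputation under a missing-at-random assumption and fixes the number: "Ten sets of imputed values will be generated to adjust for variability due to imputation". Each completed data set is analysed by standard methods and the results are pooled into one. The section names a chi-square test for binary outcomes and announces both intention-to-treat and per-protocol analyses, without saying which is primary.

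The Sample size calculation section states: "The final sample size is 144 (72 per group) after allowing a 25% attrition rate at 12-week posttreatment". The assumed cessation rates are 75% and 50%. The Primary outcome section says: "The primary end-point is 12-week posttreatment". The 25% allowance therefore applies to the outcome and time point on which the trial will be judged.

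**The concern.** Multiple imputation is itself a simulation. With few imputations, the pooled estimate, its standard error and the p-value change when the same data are imputed again from another random seed. The size of that noise depends on the fraction of missing information and on the number of imputations m. The article allows a quarter of the primary outcomes to be missing and sets m at ten. What is at stake is whether a result fairly close to 0.05 could be reproduced by someone repeating the analysis on identical data. The number ten is stated in this document, so a statistical analysis plan that followed it would inherit it.

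**Working it through.** **Inputs from the article.** m = 10; 72 randomised per arm; 25% attrition at week 16; rates 75% and 50%; alpha 0.05; power 80%.

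**Assumptions, not in the article.** Two-sided test; the imputed intention-to-treat analysis is primary; no auxiliary predictors in the imputation model; the risk difference is pooled by Rubin's rules with Barnard-Rubin degrees of freedom.

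**1. The plan's own figure.** The unpooled two-proportion formula gives n per arm = (1.96 + 0.8416)² × (0.75×0.25 + 0.50×0.50) / 0.25² = 7.849 × 0.4375 / 0.0625 = 54.9, which agrees with the stated 54 to within rounding. Inflation: 108 / 0.75 = 144. At 25% attrition, 0.25 × 72 = 18 outcomes per arm are missing and 54 are observed.

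**2. Noise by formula.** Take observed counts of 37/54 versus 27/54, a result close to 0.05.
- Total variance for large m, from the observed data: (0.685×0.315 + 0.25) / 54 = 0.00863, so SE = 0.093.
- Within-imputation variance, as if all 72 per arm were known: 0.4658 / 72 = 0.00647.
- Between-imputation variance B = 0.00863 − 0.00647 = 0.00216.
- Fraction of missing information = 0.00216 / 0.00863 = 0.25.
- Monte Carlo SD of the pooled difference = √(B/m) = √(0.00216/10) = 0.0147, about 16% of the SE.
- As a share of the SE this is √(0.25/m): 0.16 at m = 10, 0.10 at 25, 0.07 at 50 and 0.05 at 100.

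The SE also varies from seed to seed, so the test statistic varies more than this. For a result near the boundary (38/54 versus 28/54), simulation gives an SD of 0.20 at m = 10 and 0.06 at m = 100.

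**3. Effect on the p-value.** Within-arm beta-binomial imputation, with the same observed data re-imputed 20,000 times. The last column is for trials drawn at 75% versus 50%.

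| m | 37/54 vs 27/54 (p about 0.049 at large m): central 95% range of p | 38/54 vs 27/54 (p about 0.030 at large m): seeds with p ≥ 0.05 | Two seeds disagree on significance |
|---|---|---|---|
| 10 | 0.019–0.120 | 19% | 7.4% |
| 25 | 0.028–0.087 | 6% | 4.5% |
| 50 | 0.033–0.073 | 1% | 3.1% |
| 100 | 0.037–0.065 | about 0% | 2.0% |

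Repeat simulations put the 19% at 20–21%, the 7.4% at 7.5% and the 2.0% at 2.3%.

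**4. Validity.** Relative efficiency at m = 10 is 1 / (1 + 0.25/10) = 97.6%, so the SE rises by √1.025 − 1 = 1.2%. Simulated type I error at m = 10 is 5.05%. Simulated power is 75.9% at m = 10, against about 77.5–78% at m = 50–100.

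**5. Less missing information.** With about 10% missing (44/65 versus 32/65, p about 0.032), the central 95% range at m = 10 is still 0.018–0.055, and about 6% of seeds miss 0.05.

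**The case against.** The strongest reply is that ten imputations are statistically adequate. The estimate is not biased, the type I error is held and the efficiency loss is small. Near the planned effect the seed hardly matters: 40/54 versus 27/54 is significant in 99.5% of seeds at m = 10. All of this stands, and it is why the point is minor.

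The 25% is also an allowance for sizing ("after allowing a 25% attrition rate at 12-week posttreatment"), not a forecast, and mail and phone reminders are planned. Table 3 schedules dose records during treatment and cessation at week 6. If these entered the imputation model, they could lower the fraction of missing information. This stands as well, and step 5 shows that the noise is then smaller but not negligible.

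Three stronger readings are tempting, and the documents do not support them.
- A reader might infer that the primary conclusion as a whole hangs on the seed. It does so only when the result falls near 0.05; averaged over trials at the planned rates, two seeds disagree in about 7.5%.
- A reader might infer that 100 imputations cure the problem. Exactly at the boundary they do not. For 37/54 versus 27/54, 46% of seeds are significant at m = 10 and 54% at m = 100.
- A reader might infer that a missing-at-random main analysis contradicts the article's own suspicion that dropouts may include those with rebound symptoms "or those who fail to decrease consumption of benzodiazepine". It does not. The same section gives that suspicion as a reason for pattern-mixture sensitivity analyses with varying informative-missingness parameters. The exact parameter values are detail for the statistical analysis plan, which is not shown. None of this bears on the number of imputations.

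**Conclusion.** The point holds as a minor matter of reproducibility and precision. The article fixes ten imputations while allowing 25% attrition at its primary end-point, and this leaves noise of about 0.2 in the test statistic. A result with p about 0.03 would be reported as non-significant in about one seed in five. Across trials at the planned rates, the chance that two seeds disagree is about 7.5%, against about 2% with 100 imputations. Type I error is unaffected, and the cost in power is about 2 points.

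These sizes rest on a fraction of missing information of about 0.25 and on the imputed intention-to-treat analysis being the primary one. The article states neither. Lower attrition or informative predictors would reduce them.

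**What to change.** In the Statistical analysis section, and in the statistical analysis plan, replace ten with at least 50, preferably 100, imputations. State the random seed in advance, and report the Monte Carlo error of the pooled week-16 difference and of its p-value beside the results.

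A fixed seed alone is not enough: at m = 10 it makes the answer repeatable but no less arbitrary. At 50 imputations the share of non-significant seeds in the p = 0.03 example falls from 19% to 1%, and at 100 to about 0%. If the p-value lands on 0.05 itself, some seed dependence remains, and the reported Monte Carlo error will show it.

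The cost is trivial computing time and one changed sentence. No data, visits or participants are added. The change should be made and dated before the outcome data are analysed.
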